## Abstract

**Clinical trial registration:**

ClinicalTrials.gov, identifier (NCT07360626).

## Introduction

1

Musculoskeletal disorders (MSD) are among the most prevalent causes of disability worldwide and exert a profound impact on individual well-being, healthcare systems and labor productivity across diverse occupational sectors (1–3)These conditions frequently lead to chronic pain, functional limitations and reduced quality of life, contributing substantially to work absence, presenteeism and long-term disability (2, 4) Within occupational environments, a substantial proportion of these conditions are categorized as work-related musculoskeletal disorders (WMSD), which arise or are exacerbated by exposures inherent to specific job tasks and working conditions. In industrial settings, where physical workloads are often intense and repetitive, risk exposures such as awkward postures, sustained static loading and forceful or repetitive upper-limb activity markedly increase the likelihood of developing WMSD, particularly affecting the neck, shoulders and lower back (3, 5).

Manufacturing workers represent a particularly vulnerable group, as their tasks commonly involve repetitive manual operations, constrained postures, limited variation in movement and insufficient opportunities for recovery. Epidemiological evidence highlights Despite decades of research demonstrating the benefits of conservative WMSD management (especially through physical activity, patient education and self-management strategies) evidence-based recommendations are not consistently implemented in routine occupational practice (6–8). Barriers such as limited time, resource constraints, and variability in organizational support often restrict the delivery of structured preventive programs in workplaces.

International clinical guidelines underscore the importance of exercise, education and behavioral change strategies as core components in managing musculoskeletal complaints, with documented benefits in reducing pain, enhancing functional capacity and improving long-term outcomes (3, 8). Multimodal interventions combining exercise and education have shown clinically meaningful improvements in pain, mobility, psychological well-being and functional performance across a variety of musculoskeletal conditions, including knee osteoarthritis, shoulder instability and other chronic MSD (1, 9–11) Nevertheless, research focused specifically on occupational cohorts (especially those employed in manufacturing and textile industries) remains limited.

Technological innovations and the growing expansion of digital health offer new opportunities to address this gap. Hybrid rehabilitation models that integrate in-person instruction with digital health support tools, such as mobile applications, remote monitoring systems and adaptive exercise platforms, have demonstrated feasibility, acceptability and potential benefits in diverse clinical and educational contexts (9, 11, 12). These digital health platforms facilitate personalized exercise progression, improve adherence, and extend therapeutic engagement beyond face-to-face sessions. Although promising results have been reported in community and clinical populations, their implementation in industrial workplaces, where organizational, ergonomic and productivity-related constraints differ substantially, remains is still underexplored.

Textile workers face ergonomic demands associated with repetitive upper-extremity tasks, prolonged standing and high-paced production workflows. Recent epidemiological studies focusing specifically on the textile industry report a high prevalence of work-related musculoskeletal disorders, with rates frequently exceeding 60–70% among workers exposed to repetitive tasks and prolonged static postures (13, 14). The most commonly affected regions include the neck, shoulders and lower back, largely due to repetitive upper-limb movements, sustained forward-flexed postures and limited task variability (15). In addition, psychosocial factors such as high production demands, low job control and time pressure have been identified as relevant contributors to symptom persistence and chronicity in textile workers (16). Despite this, research on tailored interventions specifically designed for this sector remains scarce. Few studies have examined workplace-based programs that integrate health education with structured exercise strategies or explored the potential of hybrid delivery models that support accessibility and adherence in demanding industrial environments. The limited availability of rigorous evidence on preventive or health-promoting approaches for textile industry workers highlights the need for targeted, context-specific interventions grounded in educational frameworks that encourage safe movement, active lifestyles and sustained physical engagement.

Against this background, workplace-embedded multimodal programs that deliver both onsite health education and supervised exercise, together with home-based exercise supported by a digital app, may represent a feasible and scalable strategy to address MSD burden in manufacturing environments. Delivering the educational components and supervised exercise sessions directly at the worksite enhances accessibility and ecological validity, while the app-guided home-exercise program facilitates continuity and adherence. This integrated onsite and home model aligns with contemporary models of occupational health promotion and has the potential to mitigate symptoms, improve functional capacity and strengthen workers’ self-management skills.

The aim of this study is to examine the changes associated with an eight-week multimodal program (combining onsite health education workshops and supervised exercise with a home-based app-supported exercise intervention) on musculoskeletal pain, physical function, psychosocial outcomes, work ability and productivity among textile workers with WMSD, using a pre–post quasi-experimental design.

By integrating workplace-based education with supervised and app-guided exercise, this study seeks to provide a feasible and scalable approach to reduce the burden of musculoskeletal disorders in industrial settings. Based on current evidence on multimodal interventions and digital health support, we expect that participation in the program will be associated with reductions in musculoskeletal pain and improvements in physical function, psychosocial outcomes, work ability and productivity at post-intervention and follow-up assessments.

## Methods

2

### Study design

2.1

This study will use a quasi-experimental, single-arm, pre–post design to evaluate outcomes over time following a multimodal exercise and health education intervention among manufacturing workers. The study protocol is reported in accordance with the SPIRIT guidelines and was registered at clinicaltrials.gov (NCT07360626).

All eligible participants will receive an eight-week multimodal intervention comprising a combined exercise and health education program delivered using a hybrid format (face-to-face and online sessions). Participants will undergo a comprehensive baseline assessment performed by the research team to enable individualized exercise prescription. The same assessment protocol will be repeated immediately after intervention and at a one-month follow-up to evaluate within-participant changes in study outcomes.

### Study setting

2.2

This study will be conducted at the facilities of a medium-sized textile manufacturing company located in Zaragoza, Spain. The company operates within the industrial textile sector and includes several production-related departments such as manufacturing, quality control, logistics, and administrative services.

The intervention will be implemented within the workplace environment, facilitating integration of the program into routine occupational activities. Face-to-face assessments and workshops will be carried out on-site during working hours, while remote exercise sessions will be delivered through a mobile application.

### Participants

2.3

Participants will be manufacturing and office workers employed at the participating textile company, of both sexes, aged between 18 and 65 years, who voluntarily agree to participate and meet the eligibility criteria.

Inclusion criteria:

Current employment contract with the participating company throughout the intervention period and the one-month follow-up.Age between 18 and 65 years.Availability to attend the scheduled sessions.

Exclusion criteria:

Severe or specific musculoskeletal conditions contraindicating exercise.Current pregnancy.Concurrent physiotherapy treatment.Temporary work disability due to illness during the intervention period.Insufficient physical capacity to perform workshops or guided exercises.Cognitive or communication impairments.

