### Recruitment

2.4

Recruitment will take place at the facilities of the participating textile manufacturing company. Study information will be prepared by the research team and disseminated internally by the company’s management.

To prevent any perceived pressure from participating, company management will not be involved in participant identification, eligibility screening, informed consent, data collection or data analysis. Participation will be entirely voluntary, and workers will be explicitly informed that their decision to participate or decline would have no impact on their employment conditions or relationship with supervisors. In addition, the workers’ council (employee representative committee) was informed about the study and agreed with the study procedures, ensuring employee representation and oversight throughout the research process.

Informational meetings will be held across all work shifts to explain the study objectives and procedures and to address participants’ questions.

Following the informational meetings, workers will receive written information about the study, including contact details for the principal investigator. Those expressing interest will contact the investigator, be screened for eligibility, and provide written informed consent prior to inclusion.

A TREND-compliant flow diagram of participant enrolment is shown in Figure 1.

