#### Primary outcome

2.6.2

*Pain intensity:* Pain intensity will be measured using the Numeric Rating Scale (NRS), an 11-point validated self-reported measure widely used in musculoskeletal and occupational health research. Participants will be asked to rate their average musculoskeletal pain on a scale ranging from 0 (no pain) to 10 (worst imaginable pain) during face-to-face assessment sessions.

The NRS has demonstrated good reliability, validity, and responsiveness to change in musculoskeletal populations. Scores are commonly interpreted as: mild pain (1–3), moderate pain (4–6), and severe pain (7–10) (17).

The MCD for the NRS in musculoskeletal pain has been estimated at 1.5–2 points, which will be used to interpret the clinical relevance of pre–post changes (18). The primary outcome will be the change in NRS scores from baseline to post-intervention.

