#### Psychosocial and health-related outcomes

2.7.1

*Sleep quality:* Sleep quality will be evaluated using the Pittsburgh Sleep Quality Index (PSQI), a validated self-administered instrument that assesses sleep patterns and disturbances over the previous month across seven components subjective quality, latency, duration, efficiency, disturbances, use of sleep medication, and daytime dysfunction). The PSQI generates a global score ranging from 0 to 21 points, with higher scores indicating poorer sleep quality; a score above 5 is commonly used to identify clinically relevant sleep disturbance (28). The Spanish version of the PSQI has demonstrated adequate reliability and validity in adult populations (29).

*Depression, anxiety and stress:* Symptoms of anxiety, depression, and stress will be measured using the Depression, Anxiety and Stress Scale (DASS-21), providing separate subscale scores (0–42) for each domain. Higher score indicates greater symptoms of severity. Interpretation thresholds for each subscale are normal, mild, moderate, severe, and extremely severe. The MCD is approximately 5–6 points per subscale (30). The DASS-21 has shown good psychometric properties and has been validated in Spanish populations (31).

*Health-related quality of life:* Health-related quality of life will be measured using the EQ-5D-5L a generic questionnaire assessing five dimensions: mobility, self-care, usual activities pain/discomfort, and anxiety/depression, each with five severity levels. It also includes a visual analog scale (VAS) ranging from 0 (“worst imaginable health”) to 100 (“best imaginable health”). Higher score indicates better health status (32). The Spanish version is validated for adult populations (33).

*Work productivity and absenteeism:* Work productivity, activity impairment, and absenteeism will be assessed using the Work Productivity and Activity Impairment questionnaire (WPAI). The instrument provides four outcomes: absenteeism (% of work time missed), presenteeism (% impairment while working), overall work productivity loss, and activity impairment in daily activities outside work. Higher percentages indicate greater impairment (34). The WPAI has been validated in Spanish populations (35).

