### Statystical analysis

2.10

The statistical analysis of the quantitative data will be performed using IBM-SPSS Statistics version 29 (IBM Corp., Armonk, NY, United States). Data will be expressed as the mean and the standard deviation with a 95% confidence interval or as the median and the interquartile range. The Shapiro–Wilk test will be used to assess normality.

Given the longitudinal design with three assessment points (baseline, post-intervention, and one-month follow-up), changes over time will be analysed using repeated-measures analysis. When parametric assumptions are met, a repeated-measures ANOVA will be conducted, with post-hoc pairwise comparisons adjusted using the Bonferroni correction.

For non-parametric data, the Friedman test will be used to assess overall changes over time, with post-hoc pairwise comparisons conducted using Wilcoxon signed-rank tests, and *p*-values adjusted using the Bonferroni correction.

Effect sizes and 95% confidence intervals will be reported to quantify the magnitude of observed changes, using eta squared (η^2^) for ANOVA analyses and Kendall’s W for Friedman tests, in addition to *p*-values.

The primary analysis will follow a per-protocol approach, including only participants who attended at least 80% of the planned intervention sessions, as defined by the adherence criteria.

Statistical significance will be set at *p* < 0.05.

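### The sick-leave exclusion depends on events after enrolment, which lowers recorded absenteeism and can bias the pain change towards benefit

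*Protocol article*

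**What the plan says.** Section 2.3 (Participants) gives "Temporary work disability due to illness during the intervention period" as an exclusion criterion. Among the inclusion criteria it asks for "Current employment contract with the participating company throughout the intervention period and the one-month follow-up". Section 2.4 (Recruitment) sets the order of events: interested workers contact the investigator, "be screened for eligibility, and provide written informed consent prior to inclusion".

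The study is a "quasi-experimental, single-arm, pre–post design" (section 2.1). On the primary endpoint, section 2.6.2 states: "The primary outcome will be the change in NRS scores from baseline to post-intervention". Section 2.7.1 includes the WPAI, whose first output is "absenteeism (% of work time missed"; Table 2 schedules it at baseline, post-intervention and follow-up.

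On the analysis set, section 2.10 states: "The primary analysis will follow a per-protocol approach, including only participants who attended at least 80% of the planned intervention sessions". Section 2.2 places the workshops and face-to-face assessments on site during working hours. The limitations in section 3.1 do not mention selection through sick leave.

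**The concern.** An eligibility criterion should be decidable when a participant is enrolled. This one refers to the eight weeks that follow. Applied literally, it reclassifies a participant as ineligible because of something that happened under the intervention.

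The event is not neutral. Time off sick is part of what the WPAI measures, so dropping workers who take leave removes high absenteeism values that arose after baseline. The Introduction itself says that musculoskeletal disorders contribute substantially to work absence, so some of the leave may also mark worsening pain, and those pain scores would go too. With one arm, no comparator shares or reveals the selection. Follow-up data that are never sought from removed workers cannot be recovered later.

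**Working it through.** The plan has no figure of its own to reproduce here: it states no sick-leave rate and no relation between leave and pain. The check is therefore the timing of the criterion, followed by illustrations on stated assumptions.

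**Timing.** Screening comes before consent and inclusion (section 2.4). The criterion covers the intervention period (section 2.3). Leave already running or foreseen can be identified at screening; new leave in weeks 1 to 8 cannot. No statement in the article says that an enrolled worker who later goes on leave is kept.

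**Inputs from the article:** target sample 33; assumed minimum important difference 1.5 NRS points; SD 2.5 (all section 2.9). The SD is treated as that of the change, as the paired calculation with d = 0.60 implies.

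**Pain, simple illustration.** Assume *k* of 33 workers go on leave with pain up 2 points and the others improve by 1.5.

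- k = 2: (31 × -1.5 + 2 × 2)/33 = -42.5/33 = -1.29
- k = 3: (30 × -1.5 + 3 × 2)/33 = -39/33 = -1.18
- With those workers removed, both are reported as -1.50.

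The shift is 0.21 or 0.32 points. The standard error at n = 33 is 2.5/√33 = 0.44, so this is about half to three quarters of a standard error. The value -1.50 coincides with the planning difference in section 2.9 and the lower end of the 1.5 to 2 interpretation range in section 2.6.2.

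**Pain, varying the link.** Assume no true mean change, SD 2.5, a share q removed for leave, and correlation ρ between the tendency to take leave and worsening. The spurious mean improvement is ρ × 2.5 × φ(c)/(1 - q), where c is the normal quantile at 1 - q. For q = 10% and ρ = 0.5: 0.5 × 2.5 × 0.1755/0.90 = 0.24.

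| q | ρ = 0 | ρ = 0.3 | ρ = 0.5 | ρ = 0.8 |
|---|---|---|---|---|
| 5% | 0 | 0.08 | 0.14 | 0.22 |
| 10% | 0 | 0.15 | 0.24 | 0.39 |
| 20% | 0 | 0.26 | 0.44 | 0.70 |

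**Absenteeism.** If those removed would report 100% of work time missed and the others a%, removal lowers the mean by q × (100 - a).

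- a = 0: 2/33 = 6.1 and 3/33 = 9.1 percentage points.
- a = 3 (assumed): 4.9 points at q = 5%, 9.7 at 10%, 19.4 at 20%.

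These are upper illustrations. They need full leave inside the WPAI recall window at the post-intervention visit, and the article does not state that window.

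**Interaction with the per-protocol rule.** There are eight workshops, and 6/8 = 75% is below 80%. If attendance is judged on workshops, missing two already removes a worker from the primary analysis. Judged on workshops plus app sessions (8 + 2 × 8 = 24), the threshold is 0.8 × 24 = 19.2, so at least 20 must be completed. In either case, longer leave can exclude a worker even after section 2.3 is reworded.

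**The case against.** The best defence is that this is loose wording. Neighbouring criteria, such as current pregnancy and concurrent physiotherapy, describe status at screening, and the authors may have meant leave already running or foreseen. The article anticipates 20% attrition and reports retention, so later losses may simply count as attrition, and detailed withdrawal rules may sit in a fuller document. This is fair: removal after enrolment follows from the literal wording and is not stated as a procedure. The text does not say that screening status is meant, however, and if it is, rewording costs nothing.

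Three stronger readings are tempting and are not supported:

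- A reader might infer that everyone who worsens is excluded. The criterion covers leave for any illness, and workers who worsen but stay at work are untouched. The pain bias needs a link between leave and worsening, which is plausible but not quantified.
- A reader might infer that post-intervention absenteeism is forced to zero. Time missed without temporary work disability still counts, leave outside the recall window never entered the measure, and leave starting after the eight weeks is not covered by the criterion.
- A reader might give the contract criterion equal weight. An expected contract end date can be checked at screening, and nothing in the article links contract end to pain. It is a minor wording point.

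It also stands that absenteeism is secondary, that the pain illustration is smaller than one standard error, and that the 80% attendance rule would remove many of the same workers in any case.

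**Conclusion.** The point holds for the sick-leave criterion. As written, it makes eligibility depend on a later event that is itself part of a study outcome, in a design with no comparator. The downward bias in post-intervention absenteeism is close to mechanical for leave within the recall window. The bias in the primary pain outcome is conditional: zero if leave is unrelated to pain change, and towards benefit if it goes with worsening. On the assumed 2 or 3 of 33 workers, a mean change of -1.29 or -1.18 would appear as -1.50. Those inputs are assumptions, so they show a possible size and are not an estimate. The wording should be settled before data collection, because it determines who is followed and analysed.

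**What to change.** 1. In section 2.3, word the sick-leave criterion as status at screening. For consistency, do the same for the contract criterion (employed at screening, with an expected end date after the follow-up visit).
2. State that sick leave or contract end after enrolment does not remove a participant, that post-intervention and follow-up data are still sought, and that sick leave counts as absenteeism in the WPAI.
3. In section 2.10, state that all enrolled participants are analysed, as the main or a co-reported analysis, and align the adherence statement in section 2.5.2. Without this step the 80% attendance rule undoes much of the benefit of the first two.

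The cost is a few sentences in three sections and some assessments obtained from workers on leave. The NRS and the physical tests are planned face to face with identical procedures at each visit (sections 2.6.2 and 2.8), so a route for reaching absent workers is needed, and handgrip and sit-to-stand results may be missing for them.

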### Recruitment

2.4

Recruitment will take place at the facilities of the participating textile manufacturing company. Study information will be prepared by the research team and disseminated internally by the company’s management.

To prevent any perceived pressure from participating, company management will not be involved in participant identification, eligibility screening, informed consent, data collection or data analysis. Participation will be entirely voluntary, and workers will be explicitly informed that their decision to participate or decline would have no impact on their employment conditions or relationship with supervisors. In addition, the workers’ council (employee representative committee) was informed about the study and agreed with the study procedures, ensuring employee representation and oversight throughout the research process.

Informational meetings will be held across all work shifts to explain the study objectives and procedures and to address participants’ questions.

Following the informational meetings, workers will receive written information about the study, including contact details for the principal investigator. Those expressing interest will contact the investigator, be screened for eligibility, and provide written informed consent prior to inclusion.

A TREND-compliant flow diagram of participant enrolment is shown in Figure 1.

